### Exclusion criteria

- Patients, who didn’t successfully finish the SWABIMS Study.
- Any disease other than multiple sclerosis that would better explain the patient’s signs and symptoms
- Primary progressive MS
- Uncontrolled, clinically significant heart diseases, such as arrhythmias, angina, or uncompensated congestive heart failure.
- Uncontrolled seizure disorder
- Myopathy or clinically significant liver disease
- Medical or psychiatric conditions that compromise the ability to give informed consent, to comply with the protocol, or to complete the study
- Inability, in the opinion of the principal investigator or staff, to comply with protocol requirements for the duration of the study
- Known hypersensitivity to either Atorvastatin or Interferon-beta or other human proteins including albumin
- Known hypersensitivity to gadolinium
- Inability to undergo a MRI scan
- A history of drug abuse in the 6 months prior to enter the study
- Patients will not be permitted to take any antilipidemic medications (refer to list below). Most other medications taken for treatment of chronic conditions is permitted, as well as most medications to treat minor treatment-emergent illness(es). Given the importance of Atorvastatin metabolism by cytochrome P450 3A4, only concomitant medications permitted in the package insert will be allowed during study participation. Consistent with the package insert, the following medications are expressly prohibited throughout the study:
- All lipid-lowering medications, including niacin, fibrates (e.g., clofibrate, fenofibrate, bezafibrate, gemfibrozil), bile acid sequestrants (e.g., cholestyramine, colestipol), and HMG-CoA reductase inhibitors (e.g. fluvastatin, pravastatin, simvastatin)
- Orlistat
- Macrolide antibiotics (e.g., erythromycin, azithromycin, clarithromycin)
- Azole antifungals (e.g., fluconazole, clotrimazole, itraconazole)
- Immunosuppressive medications (e.g., cyclosporine)
- Protease inhibitors
- Nefazodone
- Fish oils
- Grapefruit juice
- Previous (before start of study) therapy with any of the following: Monoclonal antibodies, mitoxantrone, cytotoxic or immunosuppressive therapy (excluding systemic steroids and adrenocoticotropic hormone; ACTH), total lymphoid irradiation.
- Participation in any other studies (**except the SWABIMS-Study**) involving investigational or marketed products, concomitantly or within 30 days prior to entry in the study
- Treatment with drugs which might interfere with the evaluation of study drugs during the study protocol
- Likelihood of requiring treatment during the study period with drugs not permitted by the study protocol

### Removal of patients from the study

- Every patient or his/her legal representative has the right to refuse further participation in the study at any time and without providing reasons. A patient's participation is to terminate immediately upon his/her request. The investigator should seek to obtain the reason.
- The patient may be withdrawn from the study at any time at the investigator’s discretion; the reason should be documented.
- Patients who withdraw from the study will not be replaced.
- There are two different types of patient **withdrawals** that may be decided:
  1. Withdrawal from further **study participation**; *i.e*. study treatment will be discontinued and no further data will be collected for the patient withdrawn. For this type of withdrawal, before withdrawal all efforts should be made to perform all assessments scheduled for the end-of-study visit (except MRI).
  2. Withdrawal from further **study medication** without termination of study participation.

If premature termination of study medication is decided for a patient, all efforts should be made to keep that patient on the original visit schedule until the regular end-of-study visit *(i.e.*, irrespective of study medication, each randomized patient should be followed up for the originally scheduled duration).

For both types of withdrawal, the following general rules apply: as far as possible, any withdrawal of a patient should be decided only after consultation with the sponsor.

The reasons for any withdrawal are to be fully documented on the case report form (CRF).

- **Withdrawal criteria**

A patient must be withdrawn from further **study participation** under the following circumstances:

1. Withdrawal of consent: every patient has the right to refuse further participation in the study at any time and without providing reasons.
2. Participation in any other clinical trial during the duration of this study.

A patient must be withdrawn from further **study medication** under the following circumstances:

1. Non-attendance of visits

Study medication must be withdrawn if a patient does not attend two consecutive scheduled visits without a major reason agreed on by the sponsor.

1. Unauthorized use of study drug.
2. Pregnancy
   Patients who have been withdrawn from study drug treatment because of pregnancy should not undergo MRI scans while pregnant.
3. Psychiatric conditions

In the case of severe depression, suicidal ideation, or attempted suicide, study medication must be interrupted until the patient’s psychiatric condition has been fully evaluated. A psychiatrist should be consulted whenever necessary. Treatment may be resumed only after consultation with the sponsor.

A patient may be withdrawn from further **study medication** under the following circumstances:

1. Laboratory abnormality or serious/severe adverse event if dose modifications in case of toxicities don’t counteract the abnormality.
2. At the discretion of the treating physician.

The development of conditions which would have prevented a patient’s entry into the study according to the selection criteria is no reason *per se* for withdrawal. However, the withdrawal in such cases remains at the discretion of the treating physician; in these cases, consultation with the sponsor before such a decision is requested.

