## Selection of study population

### Inclusion criteria

- **Patients, who have successfully finished the SWABIMS-Study.**
- Patients with relapsing-remitting forms of multiple sclerosis (according to McDonald’s criteria)
- Patients must agree to avoid macrolids, including erythromycin and clarithromycin for the whole study duration
- Availability and willingness to continue study visits and procedures through month 12, even if discontinuation of study drug is necessary
- A woman of child-bearing potential must agree to avoid pregnancy with appropriate means while on study. Hormonal contraceptives used for more than 3 months are acceptable if therapy remains constant throughout the study
- Written informed consent
- Adequate bone marrow, renal, and hepatic function as defined in appendix.

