**Table 1. Schedule of Activities and Evaluations**

| Activities and assessments | Baseline Day 1 | Month 3   telephone | Month 6 (+/- 7 days) | Month 9   telephone | Month 12 (+/- 7 days) |
| --- | --- | --- | --- | --- | --- |
| Written informed consent | ● |  |  |  |  |
| In-/exclusion criteria | ● |  |  |  |  |
| Demographic data | ● |  |  |  |  |
| MS history | ● |  |  |  |  |
| Medical/surgical history | ● |  |  |  |  |
| Physical examination | ● |  | ● |  | ● |
| Medication history | ● |  |  |  |  |
| Lab evaluation | 1,2 |  | 1 |  | 1,2 |
| Pregnancy test | ● |  |  |  |  |
| Urinalysis | ● |  |  |  | ● |
| Vital signs | ● |  | ● |  | ● |
| ECG | ● |  |  |  | ● |
| EDSS scoring | ● |  |  |  | ● |
| MSFC scoring | ● |  |  |  | ● |
| MRI | ● |  |  |  | ● |
| Drug accountability |  |  | ● |  | ● |
| Concomitant medication | ● | ● | ● | ● | ● |
| Adverse events |  | ● | ● | ● | ● |

Lab evaluation (s. 8.2.2):

1. Serum Chemistry, Serum lipids, Hematology, Creatine phosphokinase, Thyroid Profile
2. Immunology (2 serum-probes):

- Neutralizing Antibodies (Nab), Anti-MOG-, anti-MBP-Antibodies

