### Procedures at baseline:

- Demographic data
- Inclusion and exclusion criteria
- Medical and surgical history
- MS history
- Medication history
- The contraceptive method used will be recorded, and if applicable, the age at menopause. Patients of childbearing potential will be instructed to discontinue study medication if they become pregnant and immediately notify the treating physician.
- Informed consent signature
- Vital signs
- Neurological examination by Evaluating Physician: EDSS
- MSFC scoring by Evaluating Physician or study nurse
- Physical examination
- Laboratory evaluations (Serum Chemistry, Serum lipids, Hematology, Urinalysis, Creatine phosphokinase, Thyroid Profile, Immunology (2 serum-probes stocks): Neutralizing Antibodies (Nab), Anti-MOG-, anti-MBP-Antibodies
- Pregnancy Test in women
- ECG
- MRI scan

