## Treatment phase

The treatment phase begins at the Baseline visit (visit month 15 of the SWABIMS-Study) and terminates at months 12 visit.

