### Month 6 visit (+/- 7 days)

- Physical examination
- Vital signs
- Drug accountability
- Concomitant medication
- Adverse events
- Laboratory testing:
  1. Serum Chemistry, Serum lipids, Hematology, Creatine phosphokinase, Thyroid Profile

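### The only scheduled pregnancy test is on Day 1, so an unrecognised pregnancy can reach the Month 12 contrast scan untested

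*Protocol*

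**What the plan says.** **Rules on pregnancy.** Section 7.1.3 (Removal of patients from the study) lists pregnancy among the circumstances in which study medication must be withdrawn. It continues: "Patients who have been withdrawn from study drug treatment because of pregnancy should not undergo MRI scans while pregnant". The inclusion criteria (7.1.1) add a preventive condition: "A woman of child-bearing potential must agree to avoid pregnancy with appropriate means while on study". Sections 8.3.4 and 10.1.1 tell women to stop the drug and inform the treating physician if they become pregnant.

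**Testing.** Serum beta-HCG is a defined laboratory measurement (8.2.2). In Table 1 the row "Pregnancy test" is marked at Day 1 and nowhere else. The baseline list in 10.1.1 agrees ("Pregnancy Test in women"). The Month 6 laboratory list is "Serum Chemistry, Serum lipids, Hematology, Creatine phosphokinase, Thyroid Profile". The lists for Month 12 (10.2.2), the Month 3 and 9 telephone calls (10.2.3) and unscheduled visits (10.2.4) contain no pregnancy test either.

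**Scanning.** Under 8.4 all patients have MRI at study entry and Month 12. Section 15.1.3 sets the contrast dose at 0.2 mmol/kg gadobutrol. The preparation steps in 15.1.2 include a general check that the patient is able to have the scan; pregnancy is not named.

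**Patients off drug.** Section 7.1.3 says that "irrespective of study medication, each randomized patient should be followed up for the originally scheduled duration", and the inclusion criteria require "Availability and willingness to continue study visits and procedures through month 12, even if discontinuation of study drug is necessary".

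**The concern.** Two safety rules depend on knowing that a patient is pregnant, yet after Day 1 no scheduled procedure looks for it. The baseline scan belongs to a visit that has a test. The Month 12 scan, a year later, does not. Contraception lowers the chance of pregnancy, and the duty to notify works once the woman knows, but neither detects an early pregnancy that she is unaware of. At stake is a contrast scan in a situation that 7.1.3 evidently means to avoid and, to a smaller extent, some weeks of further study drug before recognition.

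The timing of tests and scan precautions belongs in the protocol's schedule of activities. A statistical analysis plan would not supply it.

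**Working it through.** The protocol gives no figure to reproduce. The check compares the schedule with the rules and then sizes the event.

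**1. Tests against contacts.** Table 1 has five scheduled contacts: Day 1 and Months 3, 6, 9 and 12. A pregnancy test is marked at 1 of 5, and at 0 of the 4 after baseline. Two scans are scheduled; the first shares its visit with a test and the second does not. The visit lists in section 10 agree with Table 1, so this is not a damaged table.

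**2. How far the scan can fall from the Month 12 visit.** The visit window is ±7 days (10.2.2), and the scan should be within 14 days of the scheduled visit (8.4).
- If the 14 days run from the visit as held, the gap is at most 14 days.
- If both windows run from the nominal date, it is at most 7 + 14 = 21 days, in either order.
- A rejected scan may be repeated up to 14 days later (15.1.7), giving 14 + 14 = 28 or 21 + 14 = 35 days.
- After high-dose corticosteroids the scan waits until 30 days after treatment (8.4).

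On any reading, a test on the visit day may not cover the scan. The test has to be tied to the scan.

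**3. Expected number at the Month 12 scan.** The protocol gives only the total of about 60 patients. The sex split, conception rate and time to recognition are assumptions.
- Women, assumed 60 to 75%: 60 × 0.60 = 36; 60 × 0.75 = 45. This counts all women, so it overstates those of child-bearing potential.
- Conceptions in the year, assumed 1 to 5%: 36 × 0.01 = 0.36; 45 × 0.05 = 2.25.
- Unrecognised at the scan, assuming conceptions spread evenly over 52 weeks and recognised after 4 to 8 weeks: 0.36 × 4/52 = 0.03; 2.25 × 8/52 = 0.35.

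**4. What a Month 6 test would add.** On the same assumptions it finds only conceptions in the 4 to 8 weeks before it: 4/52 = 8% to 8/52 = 15% of the year's conceptions, again 0.03 to 0.35 women. Each would stop drug some weeks earlier than otherwise. A Month 12 test does nothing for drug exposure, because "The treatment phase begins at the Baseline visit (visit month 15 of the SWABIMS-Study) and terminates at months 12 visit".

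**5. Price of a positive pre-scan test.** One lost Month 12 scan is 1/60 = 1.7% of the planned primary-endpoint scans. The expected loss is 0.03 to 0.35 scans, fewer than one.

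**The case against.** The best defence is that nothing here is contradictory. The protocol never promises repeat testing. It relies on agreed contraception, a duty to stop and report, contact every three months and a treating physician responsible for safety, and nothing bars a test when pregnancy is suspected. Withdrawing known pregnancies without serial testing is a coherent policy. The expected count is well below one and rests on outside assumptions, and the protocol gives no fetal-risk figure for atorvastatin, interferon-beta-1b or gadobutrol. The patient information pages were not available, so what women were told about pregnancy and MRI cannot be judged.

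Most of this stands: it makes the point one of design and limits its weight. It does not remove the gap, because none of those safeguards detects a pregnancy that the woman does not know about.

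Three stronger readings are tempting, and the protocol supports none of them.
- A reader might infer that a Month 6 test cuts drug exposure from 12 months to 6. Those figures are intervals between tests. Exposure in a pregnancy ends when it is recognised and the drug is stopped, so the gain is a matter of weeks in very few women.
- A reader might take 21 days as the settled visit-to-scan gap. It holds only if both windows run from the nominal date; otherwise the gap is 14 days.
- A reader might infer that a woman who stopped drug for another reason and then became pregnant must still be scanned, since the MRI sentence covers only those withdrawn because of pregnancy. She remains bound to avoid pregnancy and undergoes the general pre-scan check, and nothing directs the scanning of a patient known to be pregnant. The purpose of the rule is clear; the wording is merely too narrow.

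**Conclusion.** The gap is confirmed from the protocol alone: a rule that bars MRI for patients withdrawn because of pregnancy, a single scheduled test on Day 1, and a contrast scan about a year later with no test before it. A site in full compliance can scan an unrecognised pregnancy.

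The size is small: about 0.03 to 0.35 expected cases in the trial, given 36 to 45 women, 1 to 5% conceiving in the year and recognition after 4 to 8 weeks, none of which the protocol states. The case for change rests on the protocol's own rules and on the low cost, not on that count. The Month 6 gap is real but of low yield, and the limited wording of the MRI rule needs only clarification. The efficacy conclusions are unaffected. The change should be made as a modest safety improvement.

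**What to change.** 1. **Main change (Table 1, 10.2.2 and 15.1.2).** For women of child-bearing potential, require a negative pregnancy test shortly before contrast, preferably on the same day, at the Month 12 scan and at any postponed or repeated scan. A urine test is enough. Tie it to the scan and not to the visit.
2. **Optional addition (Table 1 and 10.2.1).** Add serum beta-HCG to the Month 6 blood draw, described as a check for pregnancies not yet recognised at that time.
3. **Clarification (7.1.3).** State that no patient known to be pregnant has a study MRI, whatever the reason for stopping study medication and whether or not it has been stopped.

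The cost is one or two inexpensive tests per woman concerned, with an occasional repeat when a scan is postponed or redone. No new visit or blood draw is needed: blood is already taken at Month 6, urinalysis is already scheduled at Month 12, and beta-HCG is already a listed assay. Rarely, a positive test will cost a Month 12 scan, in line with what 7.1.3 already intends for patients withdrawn because of pregnancy.

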## Treatments

The investigator should maintain adequate records of the receipt and disposition of all study drugs supplied. Any unused medication will be returned to the sponsor at the end of the study. The investigator shall be responsible for ensuring that the study medication is stored in a cool, secure, limited access area, protected from extremes of light, temperature, and humidity.

All drug supplies, including any commercially available background and/or comparator drugs, must be stored in accordance with the manufacturers’ instructions. Study drug supplies must be stored separately from normal hospital/practice stocks. Until dispensed to the subjects, the study medication will be stored in a securely locked area, only accessible to authorized personnel.

### Investigational products

#### Interferon-beta-1b (Betaferon, Betaseron, Schering)

Interferon-beta-1b (Betaseron, Betaferon) is a non-glycosylated recombinant human interferon-beta approved for high-frequency, subcutaneous (sc) administration in the treatment of multiple sclerosis. In a randomised, double-blind trial in patients with relapsing-remitting MS (RRMS), interferon-beta-1b 250 micro g (8 million International Units [MIU]) every other day reduced the annual relapse rate and increased the proportion of relapse-free patients compared to placebo. It also reduced relapse severity, hospitalisations, and disease activity assessed by magnetic resonance imaging (MRI), and lengthened the time to a first relapse (5). The effect of interferon-beta-1b as seen on MRI in relapsing remitting multiple sclerosis was an approximately two-third reduction of disease activity.

#### Atorvastatin (Sortis, Pfizer)

**Chemical name:** Atorvastatin calcium is [R-(R*, R*)]-2-(4-fluorophenyl)-β,δ-dihidroxy-5-(1-methylethyl)-3-phenyl-4-[(phenylamino)carbonyl]-1H-pyrrole-1-heptanoic acid, calcium salt (2:1)

**Dosage form:** oral tablets

**Strength:** 40 mg

Atorvastatin is a selective, competitive inhibitor of HMG-CoA reductase, the rate-limiting inhibitor enzyme that converts 3-hydroxy-3-methylglutaryl-coenzyme A to mevalonate, a precursor of steroids, including cholesterol. Cholesterol and triglycerides circulate in the bloodstream as party of lipoprotein complexes. With ultracentrifugation, these complexes separate into HDL (high-density lipoprotein), IDL (intermediate-density lipoprotein), LDL (low-density lipoprotein), and VLDL (very-low-density lipoprotein) fractions. Triglycerides (TG) and cholesterol in the liver are incorporated into VLDL and released into the plasma for delivery to peripheral tissues. LDL is formed from VLDL and is catabolized primarily through the high-affinity LDL receptor.

### Treatment groups

#### Group 1 (Atorvastatin)

SWABIMS Study: After a treatment period of three months with Interferon-beta-1b 250 micro g (8 million International Units [MIU]) subcutaneously every other day, oral Atorvastatin (40 mg/d) was administered in addition for 12 months.

**SWABIMS Follow up Study:** The treatment withInterferon-beta-1b (subcutaneous every other day) and oral Atorvastatin (40mg/d) will be continued immediately after the end of the SWABIMS Study for 12 month.

#### Group 2 (No Atorvastatin)

SWABIMS Study: Interferon-beta-1b 250 micro g (8 million International Units [MIU]) was administered subcutaneously every other day as indicated by the manufacturers’ instructions for 15 months.

**SWABIMS Follow up Study:** The treatment withInterferon-beta-1b (subcutaneous every other day) will be continued for 12 months.

### Method of assigning patients to treatment groups

The treatment groups will be the same as in the SWABIMS-Study. Each patient continues the medication he/she received in the SWABIMS Study.

### Blinding

This is a rater-blinded study. All patients and the treating physician will be aware whether Atorvastatin is added to the Interferon-beta-1b therapy or not.

Treatment will be administered by the “treating physician” (TP). He/she will acknowledge the treatment administered, he/she will be responsible for patient eligibility, for treatment of adverse events, and for safety examinations.

”Examining physicians” (EP) will be responsible for disability scoring (EDSS, MSFC). They will not be informed whether patients are receiving Atorvastatin or not. Results of scoring will be recorded in a separate sheet. The EP will not acknowledge the treatment groups. Safety issues and other questions should not be discussed between TP and EP. Patients and TP should be informed not to discuss any safety questions with the EP.

In addition, the MRI evaluations will be performed with readers blinded to the treatment group.

Unblinding of the evaluating physician or his/her staff should generally be avoided. Single case unblinding is allowed when the actual treatment must be revealed in order to influence urgent medical care.

### Prior and concomitant therapy

Concomitant therapy with NSAID’s or acetaminophen will be at the investigator’s discretion. During the study if a patient experiences an exacerbation of symptoms related to his/her underlying MS, treatment can be given at the discretion of the treating physician. Use of medications to treat conditions unrelated to MS is allowed and will be administered at the discretion of the investigator.

### Relapse

#### Relapse definition/assessment

**All** of the following criteria (1. to 3.) have to be met for a relapse to be established:

1. neurological abnormality, either newly appearing or re-appearing, with abnormality specified by both
   1. neurological abnormality separated by at least 30 days from onset of a preceding clinical event
   2. neurological abnormality lasting for > 24 hours
2. Absence of fever or known infection (fever = > 37.5°C)
3. objective neurological impairment, correlating with the patient`s reported symptoms
   1. increase in at least one of the functional systems of the EDSS score
   2. increase of the total EDSS score

The occurrence of fatigue, mental symptoms, and/or vegetative symptoms without any additional symptom will not be classified as a relapse.

